#### Recruitment of patients

After GPs and nurses from the 23 health centres agreed to join the study, eligible patients were provided with information about the study and were invited to participate and sign a written informed consent form. Additionally, the patients from the IG were given a "Patient information sheet" with detailed information concerning the telemonitoring intervention.

### Study variables

#### Initial assessment and baseline data

The following *socio-demographic data *will be collected for every patient taking part in the study: health centre, assigned GP and nurse, date of birth and age, gender, living arrangements, main caregiver and relationship with the caregiver, level of education and the existence of any adverse social factors (*i.e*.: poverty, social exclusion, loneliness, lack of support, isolation, recent widowhood).

The following *clinical variables *will also be recorded: main disease (HF and/or CLD), degree of severity of the disease (based on the FEV1 - forced expiratory volume in one second- for COPD and on the NYHA - New York Heart Association- classification and the ejection fraction for HF. Severity of illness measures will be collected at the moment of enrolment from the clinical records depending on availability and will be used to ensure comparability between the two groups), requirement for home oxygen therapy, name and list of the drugs taken regularly, adherence to the prescribed medication (compliance) using the four-item self reported scale proposed by Morinsky *et al. *[21], the Barthel Index (BI) [22], the EuroQol questionnaire (EQ-5D) [23-25], and the Zarit Burden Interview (ZBI) [26-28].

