#### Randomisation

We used a stratified random sampling by disease (HF, CLD or both), which consisted of the random selection of patients for allocation to the control and intervention groups from three containers holding the codes of the initial patients. Subsequent draws were made to maintain the 1:1 ratio between the two study groups and between the three different strata considered.

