### Sample size

Thirty patients will be recruited in each of the study groups, the main constraints being the number of available devices and the number of potential patients fulfilling the inclusion criteria in the Bilbao Primary Care Health Region. Thus, if 30 patients are included in each group, and a 10% loss to follow-up is assumed at 12 months (based on previous analysis of mortality and other causes of loss in patients with similar characteristics), we have estimated a statistical power of 72% to detect significant differences between the CG and the IG in the mean number of total admissions with a level of significance of 5%. For the power calculation, it has been assumed that the mean number of admissions in the CG is 3.5, the standard deviation 1.7, and there will be a 35% decrease of hospitalisations in the IG with respect to the CG [32-34]. The power calculations have been performed with the sample size calculation software Ene 2.0.

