#### Analysis of the main outcome measure and impact on the use of the health care services

Firstly, at 3, 6 and 12 months follow-up, a descriptive analysis of the primary and secondary outcome measures will be carried out in the two study groups (number of hospital admissions, duration of the hospital stay and mortality rate). The variables related to the use of health care services, clinical efficacy, functional status of the patients (BI), the health related quality of life -HRQL- (EQ-5D) and the family/caregiver burden (ZBI) will also be analysed. Additionally, given that certain variables will have different follow-up periods, the incidence-rates of certain variables, such as mortality, hospital admissions, visits and episodes of worsening will be calculated.

Subsequently, both primary and secondary outcome measures will be compared between the two groups of patients at each follow-up point to test whether significant differences exist. Any changes in the functional condition (BI) or HRQL of the patients (EQ-5D) and caregiver burden (ZBI) with respect to the baseline levels will also be assessed at 3, 6 and 12 months (*i.e*., difference between the follow-up and initial scores). Quantitative variables will be compared using the Student t-test or the non-parametric Mann Whitney U test, while qualitative variables will be assessed using the Chi-Square or Fisher's exact tests. The Student's paired t-test will be used to compare the differences between the baseline scores on the BI, the EQ-5D and the ZBI and the scores obtained at 3, 6 and 12 months follow-up, for each group of patients.

If statistically significant differences are detected between the CG and the IG for the baseline characteristics analysed, the comparisons of the main outcome measures will be adjusted by the corresponding baseline variables. A logistic regression model will be used to compare dichotomous categorical variables (such as, mortality), while a general linear model will be used for quantitative variables (such as, the duration of hospital stay). In the latter case, the dependant variable will be appropriately transformed if it does not fit the normal distribution. Finally, multilevel analysis will be performed to test the effect of the individual primary care professionals involved and the clinical practice site on the results.

Whenever possible, the number needed to treat (NNT) will be calculated for the primary outcome variable (number of hospital admissions).

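### The significance-triggered adjustment rule covers severity measures planned for only some disease strata, so an adjusted main comparison could lose the HF-only or the CLD-only stratum

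*Protocol article*

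**What the plan says.** Four parts of the protocol article bear on this.

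- **Initial assessment and baseline data.** Degree of severity is based on FEV1 for COPD and on NYHA class and ejection fraction for HF. The values are collected at enrolment "from the clinical records depending on availability and will be used to ensure comparability between the two groups".
- **Randomisation.** Disease defines the strata: "We used a stratified random sampling by disease (HF, CLD or both"). Stratum sizes are not given.
- **Description of the baseline characteristics of the patients.** Baseline clinical data are compared between arms, with significance set at p < 0.05.
- **Analysis of the main outcome measure and impact on the use of the health care services.** Both arms are first compared by t-test or Mann-Whitney test. If a baseline characteristic differs significantly, "the comparisons of the main outcome measures will be adjusted by the corresponding baseline variables". Quantitative outcomes then use a general linear model. Severity is not exempted.

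The section on the primary outcome describes CLD as wider than COPD: it includes asthma and other respiratory conditions. No severity measure is named for CLD other than COPD.

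**The concern.** A rule that says to adjust for whatever differs works only if the variable can be observed in every patient. Here it cannot. FEV1 is not a planned measurement in a patient with HF alone, and NYHA class and ejection fraction are not planned in a patient with CLD alone. These are not sporadic gaps in the record. They follow the randomisation strata by design, and incomplete records add further gaps within each stratum.

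If FEV1 enters a general linear model as measured and the software keeps only patients with a value, the HF-only stratum leaves the model. With NYHA class or ejection fraction, the CLD-only stratum leaves. With FEV1 and a heart measure together, only patients with both diseases can remain. The population of the adjusted comparison would then depend on which severity measure happened to differ and on whose record held a value. The rule calls for that comparison exactly when the arms look unbalanced, which is when readers will lean on it.

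**Working it through.** **Inputs, all from the Sample size section**

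- Patients: "if 30 patients are included in each group, and a 10% loss to follow-up is assumed at 12 months", so 30 × 0.9 = 27 per arm.
- Control arm: "the mean number of admissions in the CG is 3.5, the standard deviation 1.7".
- Effect: "there will be a 35% decrease of hospitalisations in the IG with respect to the CG", so 0.35 × 3.5 = 1.225 admissions.
- Test level: "with a level of significance of 5" per cent. Sidedness is not stated, and two-sided is assumed.
- Stated result: "we have estimated a statistical power of 72" per cent.

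**Step 1: reproduce the stated power.** The noncentrality is 1.225 / (1.7 × √(2/n)). With n = 27 this is 1.225 / (1.7 × 0.2722) = 2.65 on 52 degrees of freedom. The two-sided t-test then has power 73.8%. With the Mann-Whitney efficiency factor 3/π (effective n = 25.8 per arm) it is 71.8%. The stated 72% is therefore reproduced, and the t-test figure of 73.8% is the reference below.

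**Step 2: chance that severity triggers the rule.** Under randomisation, one severity test at 0.05 triggers with probability 5%. For three tests (FEV1, NYHA class, ejection fraction), if independent, the probability is 1 − 0.95³ = 14.3%.

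**Step 3: power of the adjusted comparison if patients are lost.** This assumes the raw measure as covariate and complete cases. The difference and SD are held fixed, so any precision gained from the covariate is ignored. Because stratum sizes and data availability are not given, the retained share is an assumption and is shown as a range.

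| Share retained | n per arm | Power (t-test) |
|---|---|---|
| 100% | 27 | 73.8% |
| 80% | 21.6 | 63.8% |
| 67% (one of three equal strata lost) | 18 | 55.6% |
| 50% | 13.5 | 43.7% |
| 33% (only patients with both diseases, equal strata) | 9 | 30.1% |

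The half-width of the 95% confidence interval is t(0.975) × 1.7 × √(2/n). It is 0.93 admissions with n = 27, 1.15 with n = 18 and 1.70 with n = 9.

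**Step 4: average effect.** This takes equal strata and independent tests.

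- The worst row needs FEV1 and at least one heart measure to be imbalanced: 0.05 × (1 − 0.95²) = 0.05 × 0.0975 = 0.005.
- Any other trigger has probability 0.143 − 0.005 = 0.138.
- Average power is 0.857 × 73.8% + 0.138 × 55.6% + 0.005 × 30.1% = 71.1%.

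That is 2.7 points below 73.8%. The loss is large when it occurs, but it seldom occurs by chance.

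**The case against.** A reader might infer that following the plan will remove whole strata from the primary analysis. The text does not support that. Three conditions must all hold: a significant imbalance in a severity measure, entry of the raw measure as covariate, and complete-case fitting. The first has probability of at most about 14% by chance on the figures above. The second is not settled, because degree of severity based on these measures can also be read as a single grade derived from whichever measure suits the patient's disease. The third is not stated at all, and handling of missing covariates is normally left to an analysis plan, which is not shown here. The t-test or Mann-Whitney comparison of admissions is also planned, needs no severity value and keeps every patient. Nothing says that the adjusted model replaces it.

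It would also be wrong to say that most patients cannot have these measures. With equal strata, two thirds could have FEV1 (if all their CLD were COPD) and two thirds could have NYHA class or ejection fraction. The average power loss is under 3 points.

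All of this stands, and it limits the point to a conditional one. It does not remove it. The difficulty is not silence about missing data: the article fixes an adjustment rule that does not fit the variables it also fixes. An FEV1 that was never planned for an HF-only patient is not a missing value in the usual sense, so ordinary missing-data methods are not a natural repair. A common severity grade would help, but none is defined. It would still lack a basis for CLD other than COPD and for unrecorded values, and it would need a rule for patients with both diseases.

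**Conclusion.** The point holds in conditional form. As written, the rule could produce an adjusted main comparison without the HF-only or the CLD-only stratum, and without patients whose records hold no value. It would do so only if a severity measure triggers adjustment, enters as measured and is fitted on complete cases. The unadjusted comparison is unaffected.

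The trigger has a chance probability of 5% for one test and up to about 14% for three independent tests. If it happened, power in the adjusted comparison would fall from about 74% to between about 64% (80% retained) and 30% (33% retained). These figures rest on a two-sided 5% t-test, on assumed retention, and on the Sample size section's difference and SD holding in the retained patients with no precision gained from the covariate. The change in population matters more than the average loss of power, which is small. This is worth correcting, because the rule as stated is avoidable and a better one is available at little cost.

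**What to change.** Remove FEV1, NYHA class and ejection fraction from the significance-triggered adjustment. Adjust the main comparison for the randomisation stratum (HF, CLD, both) and for baseline variables defined for every patient. The Barthel Index is one example, since it is already collected at baseline. The number of admissions in the previous year is another, provided the count is recorded: the article uses it as an eligibility threshold but does not list it among the baseline data.

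Report the three severity measures by arm within disease stratum, as description. If severity is to be adjusted for, enter one severity category nested in stratum, with a level for unknown, so that no randomised patient leaves the model.

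The cost is a change of wording. No new measurement is needed, apart from keeping the prior-year count if it is chosen. The downside is that severity is adjusted for more coarsely than by the raw measures.

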#### Outcome measures

All the outcome measures will be collected after 3, 6 and 12 months of follow-up, except for satisfaction with the telemonitoring technology, which will be measured only once (approximately after 3 months from the start of the study). Table 2 shows a summary of the outcome variables that will be evaluated in the present study.

**Table 2 T2:** Summary of the outcome measures analysed in the study.

	Primary outcome measure	Secondary outcome measures
**Mortality**		- Mortality due to any cause
		- Mortality due to HF or CLD
		
**Use of health care resources**	- Hospital admissions due to any cause	**- **Hospital admissions due to HF or CLD
		- Duration of hospital stay
		- Emergency department visits
		- Home visits by GP or nurses
		- Visits to primary care centres by family or caregivers
		- Telephone contacts with professionals
		- Visits to specialist doctors
		
**Clinical efficacy**		- Worsening of the patients' pulmonary and/or heart condition (number of episodes)
		
**Functional status and quality of life**		- Patient Quality of Life (EQ-5D questionnaire)
		- Functional status (Barthel Index)
		- Caregiver burden (Zarit Burden Interview)
		
**Cost-effectiveness**		- Cost-effectiveness (using QALYs)
		
**Satisfaction with the new technology**		- Degree of satisfaction of patients and health care professionals
		
**Compliance**		- Patient and provider compliance with the telemonitoring

##### 1. Primary outcome measure

*Number of hospital admissions due to any cause that occurred in a period of 12 months post-randomisation*.

The hospitalizations will be classified as due to HF, due to CLD (*i.e*., COPD, asthma and other respiratory conditions) and non-cardiorespiratory causes.

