## Methods/design

### Main characteristics of the study

#### Study design

This is a randomised controlled trial with a one-year follow-up. In the intervention group (IG), in addition to the standard practice, patients will be monitored using a telemonitoring procedure, while the control group (CG) will receive the usual care. Participants will gradually join the study over a period of six months. The recruitment period could be extended to reach the targeted number of patients. Interim data analysis will be carried out after 3 and 6 months of follow-up and the final results will be obtained at 12 months post-randomisation. Figure 1 outlines the general study design.

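### The 12-month primary count starts at randomisation, but the initial patients' codes appear to be drawn as a batch before recruitment, so for them part of the counted year may precede consent, baseline and telemonitoring

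*Protocol article*

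**What the plan says.** The primary outcome (Outcome measures, item 1) is the "Number of hospital admissions due to any cause that occurred in a period of 12 months post-randomisation". Bed-days, HF/CLD admissions and use of health resources (items 2.1, 2.2 and 2.4) also run for 12 months from randomisation. Mortality (item 2.3) is counted at 12 months with no origin given.

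The Randomisation section, in the past tense, describes a draw within three disease strata from "three containers holding the codes of the initial patients", and adds: "Subsequent draws were made to maintain the 1:1 ratio between the two study groups". Under Patient selection process, the first-phase pool was 59 potentially eligible patients, and more were to be sought progressively until the target (60) was reached. The next section, Recruitment of patients, describes information and consent, with an extra information sheet on telemonitoring for IG patients only.

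Study design says: "Participants will gradually join the study over a period of six months", and then: "The recruitment period could be extended to reach the targeted number of patients". The Outcome measures section says: "All the outcome measures will be collected after 3, 6 and 12 months of follow-up", with satisfaction as the exception.

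**The concern.** Counting from randomisation is sound when randomisation comes just before the intervention can start. A batch draw from a pre-filled container, followed by staggered recruitment, can separate the two. A patient drawn with the batch and recruited later would contribute untreated time to the counted year. In the IG that time cannot show an effect of telemonitoring, so the difference between arms shrinks towards zero. The trial has a stated power of only 72%, so even a modest lag matters.

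The economic analysis has a related exposure. Resource use is counted from randomisation, while QALYs are an area under the EQ-5D curve adjusted for baseline utility. If the baseline EQ-5D is taken some time after the draw, the costs and QALYs in the ICER would cover different 12-month periods.

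**Working it through.** **Step 1. Order of events.**

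- Patient selection process: 59 potentially eligible patients in the first phase, against a target of 60. If these are the initial patients whose codes went into the containers, the batch could make up much of the sample.
- Randomisation: codes were already in the containers when drawn, so this was not allocation patient by patient at entry.
- Recruitment of patients: described after the draw. The IG-only sheet suggests that the arm was known by the consent step.
- Description of the intervention: staff of both arms attend a workshop before the intervention, and IG staff have further system training. This is another possible source of delay.
- Study design: entry is spread over six months or more.

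No visible section dates the draw relative to consent, baseline or device start, or limits the interval. The incidence rates planned in the Statistical Analysis section deal with unequal length of follow-up. They do not remove untreated time, because a rate from randomisation still includes those months and their admissions.

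**Step 2. Reproduce the stated power.** Inputs from Sample size: 30 per arm, 10% loss, CG mean 3.5, SD 1.7, 35% reduction, 5% significance (taken as two-sided, since sidedness is not stated).

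- n per arm = 30 × 0.90 = 27
- difference = 3.5 × 0.35 = 1.225
- standard error = 1.7 × √(2/27) = 0.463
- noncentrality = 1.225 / 0.463 = 2.65, with 52 degrees of freedom
- two-sample t-test power = 73.8%

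This is within 2 points of the stated 72%. Scaling n by the Mann-Whitney efficiency of 3/π gives 71.8%.

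**Step 3. Put in a lag.** Let L be the mean number of months from draw to start of telemonitoring in the IG. Assume a constant admission rate, no effect before the start, and the same SD and n. Then difference = 1.225 × (1 − L/12).

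| Mean lag L (months, assumed) | Reduction over counted year | Difference | t-test power |
|---|---|---|---|
| 0 | 35.0% | 1.225 | 73.8% |
| 0.5 | 33.5% | 1.174 | 70.2% |
| 1 | 32.1% | 1.123 | 66.3% |
| 1.5 | 30.6% | 1.072 | 62.3% |
| 2 | 29.2% | 1.021 | 58.1% |
| 3 | 26.2% | 0.919 | 49.6% |

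The 3-month row needs every IG patient drawn on day 0 and starts spread evenly over six months (mean 6/2 = 3). If half of them were in the batch and the rest started promptly after a later draw, the mean lag is 0.5 × 3 = 1.5 months, which is the 62% row.

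**Step 4. Costs and QALYs.** If baseline falls L months after the draw, the resource-use year and the QALY year share 12 − L months: 11 of 12 at a lag of 1 month, 9 of 12 at 3 months. The article does not date the baseline EQ-5D, so this remains a possibility.

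**The case against.** The strongest reply is that the lag is inferred and never stated. Gradual entry may simply describe the later patients, found progressively and allocated in later draws, with prompt starts throughout. The container draw is described only for the initial patients. Figures 1 and 2, not available here, may show the sequence, and a condensed article may leave the interval to the full protocol. All of this stands as a limit on size. It does not remove the point, because the draw, recruitment and staggered entry as described allow an untreated lead-in and nothing visible rules it out. The Ethics approval section puts consent before participation, which does not settle whether the draw came before consent.

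Four stronger readings are tempting, and the document does not support them.

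- A reader might infer that randomisation is the wrong origin. It is the standard intention-to-treat origin, and set-up delay is part of the effect of assignment. The objective speaks of the impact of a telemonitoring intervention and does not promise a full year of exposure. The weakness is the timing of the draw.
- A reader might infer that power is really 50%. That needs every IG patient to be in the batch, whereas further draws are described.
- A reader might infer that follow-up and post-randomisation are two conflicting clocks. Study design uses both in one series of time points, so a single origin is a fair reading. The article just does not confirm it.
- A reader might infer a demonstrated mismatch of the QALY year. The baseline section ties only the severity measures to enrolment.

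It is also fair to object to re-dating everyone to the baseline visit. For patients already drawn, that would discard admissions and deaths after allocation in a trial whose participants and staff are unblinded.

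**Conclusion.** The point holds as a design weakness of uncertain size. For patients allocated in the initial batch, the counted year may include time before consent, baseline and telemonitoring, and the planned incidence rates do not correct for it. Power is about 74% with no lag and falls to 70%, 66%, 62% and 58% at mean lags of 0.5, 1, 1.5 and 2 months; 50% at 3 months is an upper scenario for the planned six-month recruitment. These figures rest on assumed lags, an effect proportional to treated time, a constant admission rate and an unchanged SD. A misaligned economic analysis is possible but not shown. The change is worth making because it is cheap and the trial has little power to spare.

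**What to change.** For every patient not yet drawn, draw the arm individually after consent and the baseline assessment, shortly before telemonitoring can start, so that randomisation and baseline coincide. State that this date is the single origin in both arms for admissions, bed-days, resource use, mortality, EQ-5D/QALYs and the 3-, 6- and 12-month points. Do not start the IG clock at device installation, since the CG has no such date.

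For patients already drawn, keep randomisation as the primary origin, record the interval from draw to baseline in both arms, and report the count from baseline only as a sensitivity analysis.

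The cost is a small change in the draw procedure, one extra recorded interval, and slightly later completion of follow-up for the last patients.
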